# Chinese pediatric *Tuina* on children with acute diarrhea: study protocol for a randomized sham-controlled trial

**DOI:** 10.1186/s13063-019-3818-1

**Published:** 2019-12-09

**Keywords:** Acute diarrhea, Pediatric *Tuina*, Randomized controlled trial

## Abstract

**Background:**

Acute pediatric diarrhea is one of the most common causes of morbidity and mortality worldwide and seriously affects the health of children. Previous studies have shown that pediatric *Tuina*, a traditional Chinese medicine therapy, has potential therapeutic benefits for acute pediatric diarrhea. However, the evidence for its effectiveness is insufficient due to the lack of high-quality clinical studies. Our aim is to evaluate the efficacy of Chinese pediatric *Tuina* for children aged 0–6 years with acute diarrhea.

**Methods/design:**

This study is a randomized, double-blind, sham-controlled trial. We will include 122 children with acute diarrhea from Dongguan Kanghua Hospital in Guangdong province, China. The patients will be allocated into either the pediatric *Tuina* group or the sham *Tuina* group in a 1:1 ratio. The treatment will last for 3 days followed by an 11-day follow-up period. Both groups will receive usual care. In addition, the experimental group will receive 15–25 min of Chinese pediatric *Tuina*, while the control group will receive 15–25 min of sham pediatric *Tuina.* Both groups will receive treatments once per day, for 3 consecutive days. Primary outcome measures are diarrhea days from baseline and diarrhea times on the third day. Secondary outcome measures are the global change rating and period of days when the stool character changes to normal. Safety assessments will be monitored during each visit.

**Discussion:**

This clinical trial is designed to evaluate the efficacy of pediatric *Tuina* for children with acute diarrhea. We expect results to provide solid evidence and support for pediatric *Tuina* as an appropriate treatment for children with acute diarrhea.

**Trial registration:**

ClinicalTrials.gov, NCT03005821. Registered on 29 December 2016.

## Background

Acute pediatric diarrhea is a common and potentially serious condition with global significance. It is a major cause of morbidity and mortality for children, especially in low- and middle-income countries [1, 2]. In 2010, there were more than 1.7 billion diarrheal episodes in children under 5 years of age. Among these, about 36 million cases progressed to severe episodes, accounting for over 700,000 deaths annually [3]. Although the number of deaths due to diarrhea fell to 499,000 globally in 2015, diarrhea remains one of the leading causes of death among children younger than 5 years [4]. While the burden is greatest in low-income populations, acute diarrhea is also a common reason for outpatient visits and hospital admissions in high-income regions and has become an important global health problem [5]. Considering the severity of pediatric diarrhea, if patients are treated in an untimely manner then repeated episodes of diarrhea can lead to undernutrition and stunted growth and can further decrease cognitive function [3]. Therefore, research on childhood diarrhea has become a priority of the World Health Organization (WHO) for achieving the United Nations’ Millennium Development Goal of reducing childhood mortality [6].

The recommended treatments for diarrhea include continued feeding or increased breastfeeding, low-osmolarity oral rehydration solution (ORS) or intravenous infusion, probiotics, zinc supplementation and antimicrobial usage for bloody diarrhea [6–9]. These therapeutic methods play important roles in the treatment of diarrhea; however, some interventions, such as zinc supplementation and ORS, are not easily accepted by children or their parents which can lead to low compliance and consequently impacting their effect [10–12]. Studies have shown that ORS takes a relatively long time to produce positive outcomes and may increase the risk of diarrhea volume [13, 14]. Additionally, antimicrobials are not recommended for routine use as overuse causes intestinal flora imbalance, drug resistance, adverse reactions and increased financial burden [15]. More effective and targeted antidiarrhea treatment methods are needed.

Pediatric *Tuina* is a form of traditional Chinese medicine (TCM) therapy in which trained practitioners manually stimulate specific acupoints of the body which are located primarily on the fingers, palms, arms, head, abdomen and back, and include points such as *bagua, banmen* and *zhongwan* [16]. It is based on TCM *zang-fu organ* theory and meridian theory and seeks to unblock meridians, promote the circulation of *qi* and blood, regulate the functions of the *zang-fu* organs, and strengthen the body’s resistance to pathogens by using various manual techniques at specified locations on the surface of the body [17]. *Tuina* manipulations include pushing, kneading, grasping, pounding, arc-pushing, and so forth. All manipulations are conducted with a light, fast, and soft touch [16].

Some randomized controlled trials (RCTs) for children with acute diarrhea have suggested a benefit from pediatric *Tuina* with few side effects [18–21]. However, the methodological quality of some RCTs is poor which may weaken the validity of their results [22, 23]. Lack of scientific rigor or external validity limits widespread application of *Tuina*. The aim of this study is to evaluate the efficacy of pediatric *Tuina* as an add-on therapy compared with sham *Tuina* in addition to usual care for children aged 0–6 years with acute diarrhea.

The study protocol was written in line with the Standard Protocol Items Recommendations for Interventional Trials (SPIRIT) 2013 statement [24]. Details are provided in Additional file 1.

## Methods/design

### Study design

The study is a randomized, double-blind, sham-controlled design. The trial will be conducted from January 2017 to September 2019 in Guangdong Provincial Hospital of Chinese Medicine and Dongguan Kanghua Hospital in Guangdong province, China. This trial will include a 3-day continuous treatment period and a follow-up period with two visits (on days 7 and 14). Eligible participants will be randomly assigned to either a pediatric *Tuina* plus usual care group or a sham *Tuina* plus usual care group in a 1:1 ratio according to a computer-generated randomized table. Figure 1 shows the flow chart of the trial. The findings of the trial will be reported in accordance with the Consolidated Standards of Reporting Statement [25] and Standards for Reporting Interventions in Clinical Trials of Acupuncture guidelines [26]. The trial has been registered at ClinicalTrials.gov (NCT03005821).

**Fig. 1 Fig1:**
[figure not shown]
Flow chart of the trial

### Participants

The participants will be recruited from Dongguan Kanghua Hospital in Guangdong province, China. All participants will complete a screening form to assess their eligibility. This study will enroll 122 children with acute diarrhea. The diagnosis of diarrhea will be based on criteria as identified by Shen and Wang [27] and the WHO [28].

### Eligibility criteria

#### Inclusion criteria

Inclusion criteria are as follows:
Children aged 0–6 yearsThe first occurrence of diarrhea within 72 hChildren who meet the acute diarrhea diagnostic criteria identified by Shen and Wang [27] and the WHO [28]Stool frequency greater than or equal to five times per dayNo concurrent involvement in any other clinical trialGuardian or parents able to coordinate care during the clinical trialWritten informed consent by the children’s guardian or parents

#### Exclusion criteria

Exclusion criteria are as follows:
A history of Chinese pediatric *Tuina* on the handsDiagnosis of cholera or malariaChildren with any of the following conditions on the area to be manipulated: phlebitis, open wound, fracture, or tissue damageChildren with any of the following complications: severe dehydration, metabolic acidosis, disorders of consciousness, seizures, twitching, shock, or azotemia

### Interventions

#### Experimental group

Patients will receive montmorillonite powder and racecadotril granules as usual care according to clinical symptoms. In addition, intravenous infusion, ORS, zinc or antibiotics will be used if the pediatrician in charge considers it necessary. Dosage will be prescribed according to the age or weight of the child.

In addition to usual care, the experimental group will also receive Chinese pediatric *Tuina* treatment for 15–25 min, once per day, for 3 consecutive days. *Tuina* manipulation will be performed by trained therapists to ensure identical *Tuina* treatment according to standard operating procedures. Treatment will be performed with the child sitting either on a bed or on a stool. Children under 2 years of age will sit on their caregiver’s lap while receiving therapy. Moderate pressure *Tuina* therapy will be provided. The child will be draped with a cloak that can cover the child’s upper body, including the upper limbs and trunk, and all manipulations will be performed under the cloak.

The standardized *Tuina* therapy prescription includes six acupoints suggested by a panel of five pediatric *Tuina* experts who have a minimum of 10 years of clinical experience in this area. Manipulation times for each acupoint will depend on age. Detailed information for acupoints, manipulation times and methods is provided in Table 1.

**Table 1 Tab1:** *Tuina* acupoints, manipulation times and methods

Age	Total times					
	*Neibagua* point-arc-push, clockwise	Small intestine meridian point-clearing	Large intestine meridian point-nourishing	*Banmen* point-kneading	Abdomen-rubbing, anticlockwise	*Qijiegu* point- pushing up
<2 years old (0–1 years old)	500	300	300	300	300	300
≥2 years old and <4 years old (2–3 years old)	700	500	500	500	500	500
≥4 years old and ≤6 years old (4–6 years old)	1000	800	800	800	800	800

#### Control group

Patients in the control group will receive the same usual care as the experimental group. In addition, the control group will receive sham pediatric *Tuina*. The therapist will use one hand to hold the child’s hand or put one hand on the child’s body while the other hand performs manipulations on the therapist’s own hand instead of the child’s hand or body. Patients will be draped with the same type of cloak as in the experimental group, and all manipulations will be performed under the cloak. Manipulation times for each acupoint will also depend on age. Sham *Tuina* will be performed for 15–25 min, once per day, for 3 consecutive days.

### Outcome assessment

Two assessors who are blind to group allocations will perform outcome assessment.

#### Primary outcomes

The primary outcome measure for diarrhea will be diarrhea days from baseline and diarrhea times on the third day. The assessment of diarrhea days refers to the period of days from baseline to the first day that diarrhea is reduced to less than or equal to two times per day throughout the treatment and follow-up period. Diarrhea times will be evaluated on the third day of intervention. In this study, we define the baseline and the first day of intervention as the same day.

#### Secondary outcomes

Secondary outcome measures include both a global change rating (GCR) and the period of days when the stool character returns to normal. The GCR will be evaluated on days 7 and 14 after baseline and describes a patient’s overall clinical state as a “global impression”, as determined by the assessor. The GCR will be based on a five-point scale as follows: much better, slightly better, unchanged, slightly worse, and much worse. The period of days when the stool character returns to normal is the number of days from baseline to the first day that the stool character returns to normal throughout the treatment and follow-up period.

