### Blinding

In this study, patients, caregivers, research staff, outcome assessors and data statisticians will be masked to assignment. However, *Tuina* therapists cannot be masked as sham *Tuina* will be practiced differently from real *Tuina*. Participants will be assigned to receive their corresponding interventions in separate rooms to avoid communication. *Tuina* therapists will not be allowed to share any information in terms of patient intervention with other researchers, including outcome assessors and data statisticians. Furthermore, therapists are prohibited from speaking with guardians or participants about group allocation information. To ensure successful blinding implementation, therapists will perform manipulations under an opaque cloak-shaped device, big enough to cover the upper body and arms of a child who is 6 years old or younger. Two narrow holes are present for therapists to insert their hands through and perform *Tuina*. The entire manipulation process will be covered by the cloak. In addition, the outcome assessors who are not aware of what kind of treatment the children received will ask the participant’s guardian to complete the questionnaire independently in a separate room during the intervention as well as the follow-up period and will not be allowed to directly communicate with the therapists during the whole study process.

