### Data collection

In this study, two data collectors will be responsible for collecting all data when the children are recruited. A printed case report form (CRF) with a three-digit identification number for each participant and electronic follow-up questionnaires will be used to record all information. Each participant will have a unique three-digit identification number that will be pre-recorded on the printed CRF. The social demographic characteristics of the participants including age, height, weight, medication history and present condition will be collected. Clinical outcomes will also be collected by outcome measurement instruments during the entire intervention and follow-up period. Participants will be appropriately compensated if they complete the entire procedure. During the intervention and follow-up period, electronic questionnaires will be sent to the participant’s guardian through WeChat. For those guardians who do not have a WeChat account, telephone surveys will be used to fill in printed questionnaires which contain the same information as the electronic version. All electronic information obtained through WeChat will be recorded on reserved sections in the CRF. AEs, if any, will also be recorded. Participants have the right to withdraw from the study at any time, for any reason.

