### Statistical analysis

Statistical analysis will be performed by trial statisticians who are blinded to the group allocation using SPSS Statistics Software 19.0 and SAS version 9.4. All statistical tests will be two sided with a significance level of 0.05. We will summarize the social demographic characteristics of the participants by groups using simple descriptive statistics. Normally distributed quantitative variables will be described by means and standard deviation and non-normally distributed variables will be described by median and interquartile range. In addition, the 95% confidence intervals will be presented when calculating the difference in means between groups. For categorical variables, numbers and percentages will be presented.

We intend to use the intention-to-treat and per-protocol approach to analyze data. For intention-to-treat analysis, all participants will be included in the analysis according to the group to which they were originally randomized, regardless of whether they complete the treatment or adhere to the protocol. For per-protocol analysis, only participants who complete the whole treatment (i.e., those who receive treatments once per day for 3 consecutive days) will be included. Between-group comparisons will be performed using two-sample *t* tests for normally distributed data and Mann–Whitney *U* test for non-normally distributed data. For categorical variables, chi-square tests or Fisher’s exact test will be used for group comparison.

Multivariable regression analysis will be performed to analyze the associations between pediatric *Tuina* and primary or secondary outcomes with adjustment for covariates including social demographic characteristics, birth characteristics, medication history, and so forth. Missing data will be imputed through multiple imputation using chained equations.

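### The plan's rule for categorical variables, the natural home of the five-level global change rating, ignores the order of its levels

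*Protocol article*

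**What the plan says.** The Secondary outcomes section of the protocol article sets the GCR at days 7 and 14 and lists its levels: "The GCR will be based on a five-point scale as follows: much better, slightly better, unchanged, slightly worse, and much worse". The rating is a global impression "as determined by the assessor". The Outcome assessment section agrees on who rates: "Two assessors who are blind to group allocations will perform outcome assessment".

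The Statistical analysis section does not mention the GCR. It gives three general rules:

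- a two-sample t test or a Mann–Whitney test, depending on whether the data look normal;
- "For categorical variables, chi-square tests or" Fisher's exact test;
- a multivariable regression, of unstated type, for primary and secondary outcomes.

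Categorical variables are to be summarised by counts and percentages. All tests are two-sided at 0.05.

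On data collection, the Blinding section says that the outcome assessors "will ask the participant’s guardian to complete the questionnaire independently in a separate room during the intervention as well as the follow-up period". The Data collection section adds that "electronic questionnaires will be sent to the participant"'s guardian through WeChat, with a telephone survey as the alternative. Neither section says whether these questionnaires contain the GCR.

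**The concern.** A scale that runs from much better to much worse carries its information in the order. Chi-square and Fisher's exact test for a 2 × 5 table ask only whether the two distributions differ in some way. Shuffling the column labels leaves the result unchanged. The efficacy question is whether children given Tuina tend to be rated better, and an unordered test spreads its sensitivity over four degrees of freedom, most of which have nothing to do with that question.

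Two things are at stake. The first is power on a secondary outcome in a trial of 122 children. The second is interpretation: a small p value from an unordered test is not in itself evidence of improvement. In addition, the same table could be taken to chi-square or to Mann–Whitney under the rules as written, and the two can disagree. That choice is best closed before unblinding.

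**Working it through.** **No figure to reproduce.** The article gives no expected GCR distribution, effect or power. The group sizes come from Sample size estimation: 51 per group before the dropout allowance and 61 per group enrolled. They are used here only as group sizes. Everything else below is assumed.

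**Step 1: does order matter to the test?** Take an invented table with 51 per group, much better to much worse: group A 30/15/4/1/1, group B 20/17/9/3/2.

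- *Chi-square.* With equal groups the statistic is the sum of (a − b)²/(a + b): 100/50 + 4/32 + 25/13 + 4/4 + 1/3 = 2 + 0.125 + 1.923 + 1 + 0.333 = 5.381 on 4 df, p = 0.25. Each term belongs to its own column, so any reordering gives the same p.
- *Mann–Whitney with tie correction.* Column totals 50, 32, 13, 4, 3 give mid-ranks 25.5, 66.5, 89, 97.5, 101. The rank sum of A is 765 + 997.5 + 356 + 97.5 + 101 = 2317, against 51 × 103/2 = 2626.5 expected. The sum of (m³ − m) over columns is 159,954, so the variance is (51 × 51/12) × (103 − 159,954/(102 × 101)) = 216.75 × 87.47 = 18,960. Then z = −309.5/137.7 = −2.25, p = 0.025.

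The same data give 0.25 or 0.025, depending on which rule is applied.

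**Step 2: how much power is lost?** For each assumed control distribution, the cumulative odds were multiplied by a common odds ratio (OR) to obtain the Tuina distribution. Example: control 50/30/12/5/3% has cumulative proportions 0.50, 0.80, 0.92, 0.97 and odds 1, 4, 11.5, 32.33. Multiplied by 2.5 the odds are 2.5, 10, 28.75, 80.83, so the Tuina cells are 71.4/19.5/5.7/2.1/1.2%.

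I simulated 40,000 trials per setting and tested each with the Pearson chi-square (empty columns dropped) and the tie-corrected Mann–Whitney test, two-sided 0.05. Power in %, chi-square / Mann–Whitney (gain in points):

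| Assumed control split (%) | OR | 51 per group | 61 per group |
|---|---|---|---|
| 30/35/20/10/5 | 2 | 27.3 / 47.4 (20.1) | 32.9 / 54.6 (21.7) |
| | 2.5 | 46.2 / 70.0 (23.8) | 55.1 / 78.0 (22.9) |
| | 3 | 63.7 / 84.3 (20.6) | 72.6 / 90.2 (17.6) |
| 50/30/12/5/3 | 2 | 23.0 / 42.1 (19.1) | 27.7 / 48.6 (20.9) |
| | 2.5 | 38.5 / 62.7 (24.2) | 47.0 / 71.1 (24.1) |
| | 3 | 53.8 / 77.3 (23.5) | 63.3 / 84.3 (21.0) |
| 80/12/5/2/1 | 2 | 10.2 / 23.3 (13.1) | 12.5 / 27.2 (14.7) |
| | 2.5 | 16.0 / 34.7 (18.7) | 19.5 / 40.5 (21.0) |
| | 3 | 22.0 / 44.5 (22.5) | 27.3 / 51.9 (24.6) |

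With no effect (OR 1), chi-square rejected in 2.7 to 4.6% of trials and Mann–Whitney in 4.8 to 5.0%. Neither test inflates type I error. In the third split chi-square is conservative because several cells are sparse, which explains part of its deficit there. Fisher's test, which the plan would use for sparse tables, was not simulated; it also ignores order.

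**Step 3: who rates?** Secondary outcomes and Outcome assessment both name the blinded assessor. Blinding and Data collection describe forms that guardians fill in, without linking them to the GCR. Study design calls days 7 and 14 visits, while Data collection describes remote contact. Read together, the rater is stated. What is not stated is the route by which the assessor forms the impression on those days.

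**The case against.** **The protocol does not send the GCR to chi-square.** This is correct. A reader might infer an explicit assignment, but the Statistical analysis section never names the GCR. Mann–Whitney would apply if the scale were scored as non-normal data, and the unspecified regression could be a proportional-odds model. A separate analysis plan may settle the matter. What stands is that the article's stated rule, on its most natural reading for five labelled categories, is a poor one for this outcome.

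**Direction would be visible anyway.** Largely true: percentages per level will be shown beside the p value. The point is only that the p value does not test direction.

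**The size rests on assumptions.** Also true. The data were generated under proportional odds, which favours an ordered test. If Tuina moved children towards both extremes, chi-square could see what a rank test misses. When nearly all children are rated much better and the effect is modest, both tests are weak (10% against 23%).

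**The outcome's rank.** A reader might treat the GCR as a key secondary outcome. The article lists two secondary outcomes without ranking them, and the GCR plays no part in the sample size.

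**The rater.** A reader might infer that the protocol contradicts itself, with some ratings by assessors and others by guardians, so that two measures are mixed. The text does not support this. Both sections that name a rater name the assessor, and no section says that the guardian questionnaire holds the GCR. An assessor could rate from a guardian's answers. Making the guardian the rater would redefine the outcome after recruitment was due to end in September 2019.

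**Conclusion.** The point holds as an inexpensive improvement in analysis, not as an error that invalidates a result. The GCR is ordered, the article names no ordinal method, and the rule that most naturally covers it discards the order. Type I error is not inflated. The cost is about 13 to 25 percentage points of power for a consistent shift, conditional on three assumed control splits, odds ratios of 2 to 3, proportional odds and 51 to 61 children per group. The true figure depends on a GCR distribution that the article does not give. How the assessor obtains the rating is a minor gap in description, and no contradiction about the rater is established.

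**What to change.** Add one sentence to Statistical analysis: the GCR at day 7 and at day 14 is compared between groups by a Mann–Whitney (Wilcoxon rank-sum) test or by proportional-odds regression, with a common odds ratio and 95% confidence interval, alongside counts and percentages per level. A proportional-odds model also supplies the adjusted analysis already planned for secondary outcomes. The choice should be recorded before allocation is revealed.

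Add one clarifying sentence to Secondary outcomes stating how the assessor obtains the rating on days 7 and 14 (in person, by telephone, or from the guardian's questionnaire). It should describe what was done and leave the assessor as rater.

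The cost is two sentences. No new data, participants or assessments are needed.
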